## Abstract

**Background:**

Mental disorders are a major public health problem and are debilitating in many nations throughout the world. Many individuals either do not or are not able to access treatment. The Internet can be a medium to convey to the community accessible evidenced-based interventions to reduce these burdens.

**Objective:**

The objective of this study is to investigate the effectiveness of 4 weeks of a Web-based psychoeducational intervention program for depressive and anxiety symptoms in the community of Selangor, Malaysia.

**Methods:**

A two-arm randomized controlled trial of a single-blind study will be conducted to meet the objective of this study. We aim to recruit 84 participants each for the intervention and control groups. The recruitment will be from participants who participated in the first phase of this research. The primary outcomes of this study are depressive and anxiety scores, which will be assessed using the Patient Health Questionnaire 9 and Generalized Anxiety Disorder 7, respectively. The secondary outcome includes mental health literacy of the participants, which will be assessed using the self-developed and adapted Mental Health Literacy Questionnaire. The psychoeducational intervention program consists of four sessions, which will be accessed each week. The depressive and anxiety symptoms will be compared between participants who participated in the psychoeducational program compared with the control group. Depressive and anxiety scores and mental health literacy will be assessed at week 1 and at follow-ups at week 5 and week 12, respectively.

**Results:**

The psychoeducational intervention program consists of four sessions, which will be accessed at each week. The depressive and anxiety symptoms will be compared between the intervention and control groups using a series of mixed ANOVAs. Depressive and anxiety scores and mental health literacy will be assessed at week 1 and at two follow-ups at week 5 and week 12, respectively.

**Conclusions:**

To our knowledge, this study will be the first randomized controlled trial of a Web-based psychoeducational intervention program for depression and anxiety in an adult community in Malaysia. The results from this study will determine the effectiveness of a psychoeducational intervention program in the management of depression and anxiety among adults in the community. If proven to be effective, the intervention can serve as a new modality to manage and reduce the burden of these disorders in the community.

**ClinicalTrial:**

International Standard Randomized Controlled Trial Number (ISRCTN): 39656144; http://www.isrctn.com/ISRCTN39656144 (Archived by WebCite at http://www.webcitation.org/6hSVhV71K)

## Introduction

Mental disorders are a major global public health problem and have a debilitating effect [1]. The burden and disability due to mental disorders are huge and yet many are still untreated and do not receive professional care [2]. Although mental disorders cause approximately 60% of unavertable burden, only a limited percentage of people receive effective treatment [3]. It is estimated that 60% of depressed individuals are not being treated [4]. This is particularly for those patients seeking cognitive behavioral therapy (CBT), which is difficult to obtain due to the insufficient mental health professionals in CBT [5] and lack of services in some geographical locations [6]. Furthermore, the stigma attached to mental health problems [7,8] and discrimination toward mental illness [7] causes many individuals to seek confidential services that assure anonymity.

Lack of psychological treatment and poor compliance with medications [8], cost of treatment, limited mobility due to illnesses [6], and lack of transportation are factors that favor the Internet as a possible medium to deliver interventions to cope with these barriers. Easy access to treatment [6] and the convenience, anonymous accessibility, and programs tailored to individuals’ needs as well as information that can be updated over time are some of the advantages of interventions delivered through the Internet as compared to the conventional method [5]. In addition to reducing the cost and time of travelling, participants are also able to access the resources at home and as often as they like [9].

Many patients report an inclination for self-help treatments. The Internet can be a medium for delivering such services and evidence shows that automated, professionally developed self-help psychological interventions can be effective [10]. Internet programs without the input of professionals can still be effective [10]. Internet interventions have been shown to reduce depression, anxiety, panic disorder, posttraumatic disorders, eating disorders, and insomnia [5]. Prevention and treatment of mental disorders, especially depression and anxiety disorders, through the Internet are increasing [10]. Several Internet-based interventions were found to reduce depression and anxiety symptoms [6,8,10-13].

A systematic review of the role of the Internet in managing depression and anxiety showed that the Internet is used as a source of information often among depressed and anxious patients [8]. Internet-based CBT programs significantly reduce the severity of generalized anxiety disorder (GAD), panic disorder, obsessive-compulsive disorder, posttraumatic stress disorder, and social anxiety disorder. The study also demonstrated that confidence of participants in managing their problems is also increased [6].

A study by Straten et al [14] of 213 participants found that self-help interventions are effective in reducing the symptoms of depression and anxiety. The study also found that those with severe baseline scores and those who completed the entire session benefit most from the program. In another study, guided self-help treatment had similar effects as face-to-face psychotherapy for the treatment of depression and anxiety [15].

A variety of psychological interventions are available for treating and managing depression and anxiety, one of them being psychoeducation. Psychoeducational interventions are educational interventions offered to individuals with psychological or physical illnesses, which are available in both active and passive forms [16].

A meta-analysis on depression, anxiety, and psychological distress showed that brief, passive psychoeducational interventions are useful to reduce depression and psychological distress [16]. Passive psychoeducational interventions are relatively cheap, easy to implement, and can be done by nonprofessionals [16]. Brief intervention programs are shown to yield positive results [17].

In another review on psychological therapies for mood disorders in adults, it was found that psychoeducation is effective in treating depression [18]. Patients with mild symptoms of depression benefit more from psychoeducation and were found to have better quality of life [19]. The study also showed that group psychoeducation is effective in the short term in reducing the scores of depression. Significant reduction in depressive symptoms through a brief mailed intervention was also demonstrated in a study by Geisner and colleagues [20]. It has also been shown that psychoeducation is effective in reducing mild-to-moderate depression [21].

A study by Mackinnon and colleagues [17] comparing the outcome of CBT and a depression information website showed a reduction in depressive symptoms in both intervention groups compared to the control group. The study also found that the effect persisted at 12 months of follow-up.

A study comparing the effectiveness of two Internet interventions found that both CBT and psychoeducation reduce depressive symptoms in the intervention group as compared to the control group [11]. The information site for depression was also found to improve the participants’ knowledge on their medical, psychological, and preference of lifestyle treatments.

Due to the importance and significance of self-management to reduce depression and anxiety, we aim to investigate the effectiveness of a 4-week Web-based psychoeducational intervention program for depressive and anxiety symptoms in the community of Selangor, Malaysia. As far as we know, there is currently no available published data on Internet-based management in Malaysia on these disorders. Therefore, this study was designed to evaluate the effectiveness and applicability of a Web-based psychoeducational intervention program in our population.

## Methods

### Study Design

A two-arm parallel randomized controlled trial (RCT) of a single-blind study will be conducted to compare 4 weeks of a Web-based psychoeducational intervention program versus a waitlist control group. This study (phase 2) is a continuation of a preliminary study (phase 1), which consisted of a cross-sectional survey to detect depression and anxiety among adults in community households in the state of Selangor, Malaysia. Selangor is one of the 13 states in Malaysia, with the highest level of urbanization. In the previous study, the cross-sectional study was conducted in three of nine districts in Selangor, namely Hulu Langat, Klang, and Sepang. The study population of this study is only representative of Selangor.

### Inclusion and Exclusion Criteria

Participants who participated in the first phase of this study will be invited to participate in this study. The inclusion criteria of this study are: (1) participants who have participated in the first phase of this study and who are still living in Selangor, (2) have access to a computer and have an Internet connection, and (3) are Internet-literate. Potential participants will be excluded if they are currently receiving any psychotherapy for diagnosed psychiatric disorders.

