### Sample Size

The sample size for this study was calculated using a formula by Lemeshow et al [29]: n=(2σ^2^[Z_1−α/2_+Z_1−β_]^2^)/([μ_1_−μ_2_]^2^).

Using a power of 80%, a confidence interval of 95%, a pooled standard deviation of 9.865, and a baseline and posttest mean score of 21.1 and 16.2, respectively, in the intervention group [11], the calculated sample size was estimated to be 64 participants. Taking into consideration a 30% dropout rate [30], the final sample size calculated was 84 participants in each group.

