Nevertheless, there are some limitations in this study. One potential limitation of this study is the nature of a Web-based program itself. The Web-based program will be restricted only to those who are literate and who have access to the Internet. Although its use will be limited to people who are computer literate and who have access to the Internet, this population is increasing significantly in Malaysia. Therefore, a great number of people will be able to access this Web-based assessment and intervention program, and use it for assessment of their own mental health and seek help when required. A second limitation is assurance cannot be made that the selected participants will complete the study by themselves. However, by having a specific username and password to log in to the system, this problem would be minimized. Another potential limitation is the short duration of follow-up to assess the effect of the intervention program. However, studies have shown that effectiveness can be shown even with shorter durations [19].

The Web-based psychoeducation program could serve as a new modality to manage mild-to-moderate depression and anxiety. Our study aims to provide better recognition and management of depressive and anxiety symptoms. It also aims to educate and create awareness about depression and anxiety in the community. Depression and anxiety are the most common mental health disorders. There is a need to develop simple, brief, and effective interventions tailored to the needs of the community to reduce the burden of these disorders.

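### Entry is open to survey respondents whatever their symptoms, so one average comparison of arms cannot support the suggested use in mild-to-moderate depression and anxiety

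*Protocol article*

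**What the plan says.** **Who enters.** Under Inclusion and Exclusion Criteria, the protocol article requires "participants who have participated in the first phase of this study and who are still living in Selangor", and that they "have access to a computer and have an Internet connection, and (3) are Internet-literate". People are "excluded if they are currently receiving any psychotherapy for diagnosed psychiatric disorders". No minimum PHQ-9 or GAD-7 score appears. Study Design describes phase 1 as "a cross-sectional survey to detect depression and anxiety among adults in community households in the state of Selangor, Malaysia". Recruitment takes as its frame the 634 of 1556 respondents who left complete contact details. Baseline scores are collected after consent and before allocation, but the text gives them no part in eligibility.

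**What is analysed.** The primary outcome is change in the PHQ-9 and GAD-7 sum scores. Statistical Analysis names a mixed between-within ANOVA over pretest, week 5 and week 12.

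**What is to be concluded.** The Abstract and the end of the Introduction set a community-level aim about depressive and anxiety symptoms. The Abstract's Conclusions say the results will determine the "effectiveness of a psychoeducational intervention program in the management of depression and anxiety among adults in the community". The Discussion says the programme "could serve as a new modality to manage mild-to-moderate depression and anxiety", and its opening paragraph also points to people with mild-to-moderate illness.

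**What the size rests on.** Sample Size uses "a baseline and posttest mean score of 21.1 and 16.2, respectively, in the intervention group", taken from a cited study, with a pooled SD of 9.865. It does not name the instrument.

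**The concern.** A household sample not selected on symptoms will probably contain people who score at or near zero on both instruments. Their scores can hardly fall. The average difference between arms then mixes people who could benefit with people who could not, in a proportion the document does not give.

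Two things are at stake. If the average shows no difference, the reader cannot tell an ineffective programme from a floor effect. If it shows a difference, the estimate belongs to the mixed sample. It does not give the size of benefit in people with mild-to-moderate symptoms, nor separate them from people with severe symptoms. The Discussion nevertheless places the programme's use in the mild-to-moderate group.

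**Working it through.** **1. The plan's own figure.** Inputs from Sample Size: difference 21.1 − 16.2 = 4.9, SD 9.865, two-sided 5% level, 80% power.

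n = 2 × 9.865² × (1.96 + 0.8416)² / 4.9² = 63.6, rounded up to 64 per arm. This matches. The final 84 is 64 × 1.3 = 83.2, rounded up. The arithmetic of the 64 is not in dispute here.

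**2. Room to improve.** Instruments gives PHQ-9 a range of 0 to 27 and GAD-7 a range of 0 to 21. Anyone scoring 0 to 4 at baseline can fall by at most 4 points, so cannot show the planned 4.9-point fall. The planning baseline of 21.1 lies above the GAD-7 maximum, so it is not a GAD-7 mean. On the PHQ-9 it would be 21.1 / 27 = 78% of the maximum.

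**3. Dilution.** Suppose a share p of participants can gain 4.9 points and the rest gain nothing. The average effect is 4.9p and the standardised effect is 4.9p / SD. With n = 64 per arm the noncentrality is (4.9p / SD) × √(64/2). Power is for a two-sided two-sample t test. The document gives no p and no expected SD for this sample, so p and the SDs of 7 and 5 are assumptions.

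| Share p | Average effect | SD 9.865 | SD 7 | SD 5 |
|---|---|---|---|---|
| 0.2 | 0.98 | 8.6% | 12.3% | 19.6% |
| 0.3 | 1.47 | 13.3% | 21.8% | 37.9% |
| 0.5 | 2.45 | 28.6% | 50.2% | 78.5% |
| 0.7 | 3.43 | 49.7% | 78.5% | 97.1% |
| 1.0 | 4.90 | 79.6% | 97.6% | above 99% |

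Worked line for p = 0.5 and SD 9.865: 2.45 / 9.865 = 0.248; 0.248 × √32 = 1.405; power 28.6%.

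To hold 80% power, the SD must shrink in proportion to p. At p = 0.5 that means 9.865 × 0.5 = 4.9, and at p = 0.3 it means 9.865 × 0.3 = 3.0.

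**4. Size of a symptomatic subgroup.** After 30% dropout, 84 × 0.7 = 58.8 per arm remain. At p = 0.2 that leaves 58.8 × 0.2 = 11.8 symptomatic people per arm; at p = 0.5, 29.4; at p = 0.7, 41.2. With 29 per arm, the 95% half-width of the difference is 1.96 × SD × √(2/29): 2.6 points at SD 5 and 5.1 points at SD 9.865. These counts start from 84 with dropout, whereas the table uses the plan's 64 evaluable.

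**5. What the background says on severity.** The Introduction cites a self-help study in which "those with severe baseline scores and those who completed the entire session benefit most from the program". It also cites a study in which psychoeducation, the approach tested here, helped mildly depressed patients more. The two point in opposite directions.

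**The case against.** The strongest reply is that open entry is a legitimate community design and fits the stated objective. The Abstract's Conclusions speak of adults in the community and do not mention mild-to-moderate illness. The Discussion's sentence is hedged and is about potential use, not a tested hypothesis. Moderator terms and subgroup cut-offs are usually left to an analysis plan, which is not shown here. All of this stands. The absence of a subgroup analysis is therefore not itself the error; the point is that the article's suggested use goes beyond what its stated population and comparison can show.

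Four stronger readings are tempting, and the document supports none of them.

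- *The trial is underpowered by a known amount.* The share who can improve is not given, and a sample bunched near zero would usually have a smaller SD. At p = 0.5, an SD of 5 restores almost all the planned power.
- *The figure of 21.1 shows that the source sample was clearly symptomatic.* It shows only that the scale was not the GAD-7. How severe 21.1 is depends on an instrument that Sample Size does not name.
- *The background says benefit rises with severity.* It points both ways, which is a reason to examine the question and not to presume the answer.
- *A positive average would say nothing about people with symptoms.* If those near zero cannot improve, a reduction in scores must come from people who have symptoms. What stays unknown is its size in them, and whether it lies in mild-to-moderate or severe cases.

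**Conclusion.** The point holds as a mismatch between the people studied, the one comparison stated and the use suggested in the Discussion (more loosely, in the Abstract's Conclusions). It does not follow that the trial cannot answer its own question: the average comparison does answer the community-symptom objective.

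A null result would be open to a floor-effect explanation. The planning effect, from an unnamed instrument, may not transfer to this sample. The cost in power cannot be fixed from the document. At a share of one half, the illustration runs from about 29% to 79% as the SD goes from 9.865 to 5, and it assumes no effect at all in the remaining half. Figure 1 is not shown, but the recruitment text describes no symptom screening.

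**What to change.** Keep eligibility unchanged.

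1. **Model (Statistical Analysis).** For PHQ-9 and GAD-7, analyse the week 5 and week 12 scores with arm, time, arm-by-time and the baseline score as covariate. This replaces the mixed ANOVA with pretest as an outcome level. Simply adding the baseline score to that ANOVA would put the same measurement on both sides of the model.
2. **Severity.** Add an arm-by-baseline-score interaction as a supportive analysis. Report the arm difference among participants at or above a baseline cut-off fixed before arm-level data are examined, with the number symptomatic in each arm.
3. **Claim (Abstract Conclusions and Discussion).** State the main conclusion as one about mean symptom scores in unselected Internet-literate adults. Tie any statement about mild-to-moderate depression or anxiety to the subgroup estimate.

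The baseline scores are already scheduled in Table 1. The article reports data collection as complete but analysis as unfinished at submission, so the change is feasible if arm-level results are still unseen. It costs a reformulated model and revised wording. The price is an imprecise subgroup estimate, perhaps on as few as 12 people per arm under the lowest share assumed, and a narrower headline claim.

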### Recruitment

A total of 1556 participants participated in the first phase of this study, entitled “Contributing Factors of Common Mental Health Disorders in Selangor.” Out of these, 634 participants provided complete contact information. This serves as the sampling frame in this study. A team of trained enumerators will visit the participants’ households to brief them about the study. Their personal particulars will be updated and their Internet literacy will be checked.

Eligible participants will be invited to participate in the study (second phase) through a phone call by a trained research assistant. They will be briefed about the study again. A respondent information sheet containing detailed information about the study, website log-in information, and a consent form will be emailed to the participants. After consenting to participate in the study, the participants will complete the baseline online assessment and then will be randomly allocated to either the intervention or the control group (Figure 1).

**Figure 1 figure1:**
[figure not shown]
Flowchart of study design.

### Randomization

A list of eligible participants who consented to participate in the study will be numbered. Using a random number table, the participants will be randomly allocated to either the intervention or the control group. This study is a single-blinded trial in which the participants will not know whether they are in the intervention or the control group. However, the researcher-in-charge will be aware of the group allocation.

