#### Emails and Text Messages

Before commencement of the program, the participants will be notified of the dates for each session through email, which will also be provided in the website log-in information site. Participants will receive notification of the commencement of each session every Monday via email and a phone call and they will be given 7 days to complete the session. First reminders via text messages will be sent every Wednesday to alert the participants to log in and complete the session. For those who do not complete the session, a second and third reminder through phone calls will be done on Fridays and Sundays. These reminders are important to enhance the compliance of the participants to the program.

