### Waitlist Control Group

Participants allocated to the control group will be blocked from the content of the intervention program. They will only be allowed to do the assessments. After the 12-week follow-up assessment, the participants in the control group will be offered to join the intervention program if they are interested and this is purely on a voluntary basis.

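### The trial is labelled single-blind, but controls are locked out of the program and participants score their own outcomes, so the primary outcomes are in effect open-label

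*Protocol article*

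**What the plan says.** The protocol article's Randomization section makes the blinding claim about participants, and about their group: "This study is a single-blinded trial in which the participants will not know whether they are in the intervention or the control group". It then adds: "However, the researcher-in-charge will be aware of the group allocation". The Abstract (Methods) and Study Design also call the trial single-blind.

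The rest of the Methods section describes the two arms as follows.

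- Study Design sets the program "versus a waitlist control group".
- Under Intervention, the program arm sees all of the website content in four weekly sessions and may use it without limit.
- Under Emails and Text Messages, each session is announced: "Participants will receive notification of the commencement of each session every Monday via email and a phone call". Text and phone reminders follow.
- Under Waitlist Control Group, what controls may reach on the site is restricted: "Participants allocated to the control group will be blocked from the content of the intervention program. They will only be allowed to do the assessments".

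The primary outcomes are changes in the PHQ-9 and GAD-7 sum scores to weeks 5 and 12, and the secondary outcome is change in the MHLQ score. The Intervention section says that participants complete the assessments online and unaided.

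**The concern.** The one blinding claim in the article concerns the people who also score the outcomes. When a primary outcome is self-reported, the participant is the outcome assessor, so participant blinding is what would protect the comparison from expectation and from differences in how symptoms are reported. If that blinding does not exist, a group difference in PHQ-9 or GAD-7 may partly reflect participants knowing that they did or did not receive a program, or the personal contact that came with it.

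A waitlist design is legitimate and its openness is usually accepted. The problem is that the label tells readers, and anyone who later rates the trial for risk of bias, that a safeguard is in place when the design does not provide it. The limitations in the Discussion cover Internet access, whether the enrolled person is the one who completes the study, and short follow-up. They do not mention reporting or performance bias.

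**Working it through.** No stated figure needs reproducing. The check sets the sections side by side and asks what each participant can observe before the outcomes are measured.

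1. **Before allocation.** Under Recruitment, participants are briefed at a household visit and again by phone, and are emailed detailed study information and a consent form. They complete the baseline assessment and are then randomized. By that order, baseline scores precede any knowledge of the arm.

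2. **Intervention arm, weeks 1 to 4.** The participant logs in, finds psychoeducational content, and is notified of and reminded about a new session each week. This person can tell that a program is being delivered.

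3. **Control arm, same weeks.** "Participants allocated to the control group will be blocked from the content of the intervention program". "They will only be allowed to do the assessments". This person logs in and finds questionnaires only. No sham or attention-control site is described that could make the two experiences look alike.

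4. **Outcome measurement.** Weeks 5 and 12 both come after steps 2 and 3. The PHQ-9, GAD-7 and MHLQ are self-completed, and no separate blinded assessor is described.

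5. **Staff.** The researcher-in-charge is stated to know the allocation.

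Steps 2 to 4 cannot be reconciled with the claim in Randomization.

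**Session contacts per intervention participant.** The inputs come from Emails and Text Messages.

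- Each week: one email and one call on Monday, and one text on Wednesday. Calls on Friday and Sunday go only to those who have not completed the session.
- Calls: minimum 1 × 4 weeks = 4; maximum (1 + 2) × 4 weeks = 12.
- Emails: 1 × 4 = 4. Texts: 1 × 4 = 4.

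The advance email listing the session dates is not counted. These contacts are tied to sessions that controls do not have. Contacts with controls about their week 5 and week 12 assessments are not described, so the net imbalance between arms cannot be calculated.

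**The case against.** Several points on the other side are fair.

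- **The information sheet and flowchart are not shown.** The article does not establish what controls were told about the waitlist or about the other arm. Participants may have been kept unaware of the study hypothesis, and disappointment at being on a waitlist is an inference. This stands, but Randomization claims blindness to group, which is a different claim and one that the lock-out undermines.
- **The later offer of the program.** A reader might infer that offering controls the program reveals their arm. The offer comes after the 12-week assessment, when all outcomes have been collected, so it cannot itself unmask anyone during measurement. The point rests on the lock-out and the sessions.
- **Nobody is blind.** A reader might infer this too. The article unblinds the researcher-in-charge and implies that the technician who registers participants by group also knows. It does not state the analyst's status, and an article commonly leaves that to the full protocol or analysis plan.
- **A share of the planned effect.** It is tempting to express the bias as a fraction of the sample-size effect, (21.1 − 16.2)/9.865 = 0.50 SD. The documents give no bias size, and the 4.9-point difference is a baseline-to-posttest change within one arm, so it is not a yardstick for a between-arm bias.
- **Reminders belong to delivery.** The article presents them as a way to improve compliance and never claims an effect of web content alone. That is right. Contact bears on how the conclusion should be worded, and its presence is not in itself an error.
- **Self-completion online avoids interviewer-rating bias.** This is true, but it does not address the participant's own knowledge of the arm.

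**Conclusion.** The single-blind statement is wrong as written. Read together, Study Design, Intervention, Emails and Text Messages and Waitlist Control Group describe a trial in which participants can recognize their arm before weeks 5 and 12. They score their own outcomes, so both primary outcomes, and the MHLQ, are in effect open-label at follow-up. This assumes only that no undescribed sham content was shown to controls, and the article says that they can do nothing on the site except the assessments.

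The size of any bias cannot be derived from the documents. The countable part is 4 to 12 calls, 4 emails and 4 texts per intervention participant, against an undescribed number for controls; 12 calls is a ceiling reached only by someone who is still incomplete on every Friday and Sunday. Sample size, endpoints and the planned model are not affected. What changes is the claim that the trial can support: an open comparison of a program with its reminders against a waitlist.

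**What to change.** 1. Remove the single-blind label from the Abstract, Study Design and Randomization.
2. State in Randomization that participants and the researcher-in-charge are not blinded, and that all outcomes are self-reported.
3. Add reporting bias and performance bias to the limitations in the Discussion.
4. Word the conclusion as the effect of the program together with its reminder contacts, compared with waitlist.

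Optionally, code the arms A and B in the data set for any analysis still to be run. The Results section says that data collection was complete at submission, and the Trial section says that analysis was not yet finished. Whether masked analysis is still possible is therefore for the sponsor to judge.

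Items 1 to 4 cost only wording and need no new data. The conclusion becomes more modest.
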